#### Interim and endline cross-sectional surveys

An interim survey in a sample of the enrolled population will be performed prior to the second fMDA cycle where participants are surveyed house to house. From the list of households enrolled at the time of the survey, a random sample of households will be selected proportional to cluster size. The final study year will conclude with an endline survey in all clusters. The goal of the surveys will be to invite new or unenrolled community members to enroll in the study to include a larger proportion of the population in the study, update demographic and clinical data from enrolled participants, and collect DBS to assess secondary trial outcomes of infection prevalence and seroprevalence. Acceptability of fMDA will also be assessed in the intervention arm. Acceptability will be assessed both quantitatively and qualitatively, in terms of refusal rates and open-ended questions in the intermediate and endline surveys.

#### Costing and cost-effectiveness assessment

Cost data will be captured in a quantitative survey provided to all participants who were diagnosed with a confirmed case of malaria by a health establishment during the trial period. The survey will be administered 15–30 days following the diagnosis to allow potential costs associated with the infection to accrue. Cost data will include direct intervention costs for the provider (e.g., Ministry of Health capital expenditures, consumables, personnel, training, transport, and infrastructure); direct costs to participants (e.g., other medications not provided free-of-charge by the interventions, transport costs); and indirect costs from the participant perspective (e.g., lost wages due to malaria per patient and companions).

#### Non-trial care

Participants will be free to seek usual and as-needed medical care at their own discretion, with no effect on study eligibility or arm allocation. Participants undergoing blood testing or receiving medication(s) will receive anticipatory guidance on potential side effects. In the event of symptoms, participants will be instructed to notify the study staff. Study teams encountering individuals with severe or uncomplicated malaria, or other acute illness, will refer such participants to the nearest health facility.

#### Data management

Data will be captured using REDCap forms on electronic tablets and uploaded daily to a secure server. When internet and/or electricity is unreliable, paper forms will be used to collect information instead of tablets. Training on how to capture electronic health data and use the tablets will be conducted before each survey and round of fMDA. Study documents will be retained for 10 years following the end of the trial.

#### Laboratory methods

##### Malaria microscopy

Participants will be instructed to seek care at local health posts whenever they have a fever, and malaria testing will be conducted by microscopic blood film examination. Blood smears will be stained with 2% Giemsa for 30 min and read by experienced microscopists. Parasite densities will be calculated from the number of asexual parasites per 200 leukocytes (or per 500, if < 10 asexual parasites/200 leukocytes), assuming a leukocyte count of 8,000/µL. A blood smear will be considered negative if examination of 100 high power fields does not reveal asexual parasites. Thin smears will be used for parasite species identification.

##### Molecular methods

Molecular diagnosis by real-time PCR will be performed following the modified protocol reported by Mangold, Manson et al. [54]. Parasite density calculations will be based on standard curves generated using clinical samples with known parasite concentration. Additionally, more sensitive methods may be used including amplification of parasitic mitochondrial DNA, which may improve sensitivity more than ten-fold compared to 18 s rRNA assays [54, 55]. The amplification of mitochondrial genes could be combined with the use of additional PCR targets to discriminate between species.

Genotyping of both the human and parasite DNA will be performed on blood samples to document G6PD and CYP2D6 genotypes in Peru, to assess within-host parasite genetic diversity, classify infections as local or imported [56], and classify *P. vivax* infections as new, recrudescent, persistent, or relapse [57]. G6PD variants previously associated with G6PD deficiency in Latin America as well as any new variants will be genotyped using long-read sequencing (Oxford Nanopore) of PCR amplicons covering 11 Kb of the ~ 18Kb gene (manuscript in preparation). Similarly, CYP2D6, variants which may impact metabolism and thus efficacy of 8-aminoquinolines, will be genotyped in a subset of participants with recurrent episodes after fMDA administration. Highly discriminative genotyping will be conducted by Illumina-based targeted deep sequencing of short, variable regions with numerous alleles (microhaplotypes) for *P. falciparum* and *P. vivax* [58–60].

##### Serological methods

Using methods described previously [61, 62], serological tests will be performed using samples from cross-sectional surveys to measure antimalarial antibodies that reflect recent and more distant exposure. Malarial antigens to assess distant exposure may include: *Pv* merozoite surface protein (MSP)−1.19, *Pv* apical membrane antigen (AMA)−1, *Pf* glutamate-rich protein-fragment (GLURP)-R2, and *Pf* AMA-1. Based on preliminary data from our cohort studies, malarial antigens to assess recent exposure may include other objectives such as, *Pv* MSP-10, *Pv* MSP-8, Pv RBP2b [63–65], and *Pf* Early transcribed membrane protein (Etramp)−5. A Gaussian mixture model will be used to determine positivity. Reversible catalytic conversion models fitted by standard maximum likelihood will be used to generate a seroconversion rate (SCR) [66, 67]. A longitudinal analysis in the same individuals will also enable study of the dynamics in malaria exposure following interventions [68].

## Outcomes and measures

### Sample sizes and power calculations

The study is designed to have 80% power to detect at least 68% relative reduction in cumulative *P. vivax* incidence for fMDA versus control over 3 years, with 15 clusters per study arm (mean population per cluster = 251), based on anticipated baseline *P. vivax* API of 65 cases/1000 population for the control arm, a coefficient of variation (*k*) of 0.87 based on past data, and a 0.05 significance level using a two-sided test [69]. As Peru is aiming for malaria elimination, this anticipated effect size is considered necessary and consistent with available evidence [18–20, 70, 71].

### Statistical analysis

#### Primary analysis

An intention-to-treat (ITT) approach will used, in which all clusters with at least one index case during follow-up will be analyzed according to their randomized intervention assignment. For the primary outcome of cumulative incidence of all microscopy-confirmed cases reported in study area residents, negative binomial regression using generalized linear models with cluster-level case counts and cluster population size as an offset will also be used to estimate cumulative incidence ratios (CIR) between study arms [70, 71]. The primary analysis will adjust for covariates used in the restricted randomization (baseline incidence, population size, distance to Iquitos, and distance to a health post) [72]. We will also perform a secondary adjusted analysis that controls for covariates used in the restricted randomization as well as baseline covariates (e.g., baseline coverage of vector control interventions) that are correlated with the outcome (likelihood ratio test *p*-value < 0.2). The secondary adjusted analysis may yield higher precision than models only adjusted for restricted randomization covariates due to any chance imbalances in baseline covariates that are associated with the outcome [73]. Comparisons of incidence measures will be expressed at the cumulative incidence ratio (CIR) or the protective efficacy (PE = 1-CIR × 100%) with their corresponding 95% confidence intervals.

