#### Identification of index cases and measurement of incidence

Malaria case information is recorded in fever books at health posts, and these cases are reported to the regional level. Index cases from the 2 years prior to trial launch and prior to each cycle of study medication administration will be geo-located prior to that cycle. Index cases also include cases detected during regular interventions by the health system and asymptomatic cases identified during study surveys.

During the trial, any participant with a fever will be instructed to seek medical care. For any new or relapse malaria cases diagnosed, a finger prick will be obtained to collect a DBS before administering treatment. A study team member will also conduct a case investigation (within 48 h of diagnosis) to confirm clinical and demographic details. If a pre-treatment sample was not obtained, study staff will aim to collect a sample from the participant within 3 days. If the new index case is an enrolled participant in the intervention arm, they will be eligible for fMDA at the beginning of the next cycle.

The primary outcome measure of cumulative incidence is the number of incident symptomatic microscopy-confirmed *P. vivax* malaria cases in residents divided by the total population. Cumulative cases will be calculated during the period from trial launch through 1 year after the launch of round 3a of fMDA. The denominator will include all the participants in the study except for those who have withdrawn from the study.

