#### Spillover effects

An effective intervention must decrease or interrupt transmission among individuals receiving the intervention (a “direct effect”) as well as among non-recipients outside of intervention zones (a “spillover effect” or “community effect”) [75–77]. There is a biological basis for spillover effects of fMDA. Chemotherapy can block transmission by reducing gametocyte biomass, and subsequent movement of humans and mosquitos can result in spillover effects outside of intervention zones. Our primary analysis at the cluster level is a pooled effect estimate across intervention recipients and non-recipients. Direct and spillover effects of fMDA will be estimated by comparing malaria incidence and prevalence in non-recipients in proximity to fMDA zones by arm. Direct effects will be defined as the cumulative incidence ratio (or prevalence ratio) among treated individuals in focal treatment zones within 200 meters of index case in the intervention arm vs. the control arm. Spillover effects will be defined as the cumulative incidence ratio among treated individuals outside focal treatment zones around index cases in the intervention arm vs. the control arm. To test for possible contamination of the control arm, using data from the endline prevalence survey, we will assess whether malaria prevalence in the control arm differs between households closer to or further from treatment clusters. We will calculate the distance from each household sampled in the endline survey to the nearest treatment cluster boundary. Then we will perform a clustered permutation test of the null hypothesis that malaria incidence and prevalence do not differ at the 20th and 80th percentiles of the distance to the nearest treatment cluster boundary, controlling for covariates used in the constrained randomization [78].

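### The primary analysis set, labelled intention-to-treat, drops any cluster with no index case during follow-up, which removes the intervention's best results and pulls the estimated effect toward the null

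*Protocol article*

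**What the plan says.** Under Statistical analysis, Primary analysis, the protocol article announces an intention-to-treat approach in which "all clusters with at least one index case during follow-up will be analyzed according to their randomized intervention assignment". The model is "negative binomial regression using generalized linear models with cluster-level case counts and cluster population size as an offset".

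The section on identification of index cases and measurement of incidence defines the outcome as incident symptomatic, microscopy-confirmed *P. vivax* cases "divided by the total population". It sets the window: "Cumulative cases will be calculated during the period from trial launch through 1 year after the launch of round 3a of fMDA". It leaves out no village for having no cases. The same section makes an index case a wider category than an outcome event: "Index cases also include cases detected during regular interventions by the health system and asymptomatic cases identified during study surveys".

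Study setting and trial preparations already excludes villages with sporadic transmission (fewer than 2 cases in the year before the trial), so that screening takes place before randomisation. Secondary analyses carries the primary approach over to the secondary incidence outcomes. Nothing in the article brings zero-case clusters back or plans an analysis of all 30.

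**The concern.** An intention-to-treat set is fixed by randomisation. This one is fixed partly by what happens afterwards, through an event closely tied to the primary outcome. If fMDA works, its villages are more likely to have no index case, so the filter removes mainly fMDA villages, and precisely the ones where it worked best.

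The design gives no reason for the filter. A rule of this kind might suit a reactive intervention that is delivered only once a case appears. Here fMDA is proactive: each cycle is triggered by index cases from the preceding 2 years. Given the entry criterion, every intervention village should have index cases for round 1a. A village with none during follow-up has normally been offered the intervention and would then be excluded for responding to it.

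At stake are an understated primary effect, lost power in a trial of only 30 clusters, and the loss from the primary comparison of the villages that come closest to elimination, which the sample size section gives as Peru's aim.

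**Working it through.** **Inputs (Sample sizes and power calculations).** 15 clusters per arm, mean population 251, control rate 65/1000 per year, k = 0.87, 3 years, 68% reduction (CIR 0.32), two-sided alpha 0.05. Assumed: gamma-distributed cluster rates with the same k in both arms.

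**The plan's own figure.** The Hayes–Bennett formula for rates, without the small-sample +1, is

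c = (1.96 + 0.8416)² × [(λ0 + λ1)/y + k²(λ0² + λ1²)] / (λ0 − λ1)²

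with λ0 = 0.065, λ1 = 0.0208 and y = 251 × 3 = 753. This gives c = 14.62, and power at 15 clusters of 81.0%. Adding 1 gives c = 15.62 and 78.3%. The stated 80% is reproduced, so these inputs are a sound basis.

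**Probability that a cluster has no case.** For gamma-Poisson counts, P(0) = (1 + μk²)^(−1/k²), with k² = 0.7569.

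- Control: μ = 251 × 0.065 × 3 = 48.9, so P(0) = 0.8%, or 0.12 of 15 clusters.
- fMDA: μ = 48.9 × 0.32 = 15.7, so P(0) = 3.4%, or 0.51 of 15 clusters.

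**Effect on the ratio.** A dropped cluster contributes no cases, so with equal cluster sizes

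CIR among kept clusters = CIR × (1 − P0 control) / (1 − P0 fMDA).

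At planning values this is 0.32 × 0.9918 / 0.9657 = 0.329. Protective efficacy (PE) of 68% reads as 67.1%. Other settings:

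| Control rate | Years | True CIR | Dropped, fMDA vs control | CIR kept |
|---|---|---|---|---|
| 65/1000 | 3 | 0.32 | 0.51 vs 0.12 | 0.329 |
| 65/1000 | 1.5 | 0.32 | 1.16 vs 0.30 | 0.340 |
| 65/1000 | 1 | 0.32 | 1.81 vs 0.49 | 0.352 |
| 65/1000 | 3 | 0.10 | 1.94 vs 0.12 | 0.114 |
| 65/1000 | 1.5 | 0.10 | 3.76 vs 0.30 | 0.131 |
| 15/1000 (assumed) | 3 | 0.32 | 2.63 vs 0.76 | 0.368 |

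The shorter periods are shown because Trial status dates recruitment from October 2024 and completion to May 2026.

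**Simulation with unequal villages.** 1,000 trials per scenario, lognormal village sizes with log-SD 0.5 limited to 40–650 (assumed), and an unadjusted negative binomial fit:

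| Scenario, 3 years | CIR, all 30 | CIR, kept | Rejection rate, all → kept |
|---|---|---|---|
| No effect | 0.993 | 0.992 | 8.3% → 9.0% |
| Uniform 68% reduction | 0.323 | 0.337 | 94.1% → 93.3% |
| 20% of fMDA villages eliminate, CIR 0.40 in the rest | 0.328 | 0.411 | 83.7% → 76.2% |
| One third eliminate, CIR 0.48 in the rest | 0.309 | 0.474 | 76.7% → 58.7% |
| Half eliminate, CIR 0.64 in the rest | 0.315 | 0.643 | 60.7% → 25.9% |

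Under the uniform 68% reduction, at least one fMDA cluster is lost in 52% of trials. In the last three rows the overall effect is held near 0.32 (for example 0.8 × 0.40 = 0.32), and the filtered analysis returns roughly the ratio in the villages that did not eliminate. The rejection rates come from a Wald test that is anti-conservative with 30 clusters. Compare them across each row, not with the planned 80%.

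**The case against.** The strongest reply is that the filter refers to index cases, not outcome events. A village with no symptomatic case but one infection found in a survey stays in and contributes a zero. The endline survey covers all clusters, and the Background describes infections in Loreto as mainly subclinical. This stands, and it makes the drop counts above upper bounds for their scenarios. If surveys raise the expected number of index cases by 50% or 100% (assumed), P(0) in the fMDA arm at planning values falls from 3.4% to 2.1% or 1.4%. That is 0.31 or 0.22 clusters, and the kept CIR is 0.325 or 0.324. The direction does not change, and entry to the primary analysis then also depends on survey detection.

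It can also be said that the bias is conservative, that it vanishes under the null, that the primary model adjusts for all four restriction covariates, and that endline prevalence would still show near-elimination. All of that is fair. It means there is no threat to the type I error, that lost balance is partly repaired, and that successes are hidden only in the incidence analyses. It gives no reason to drop randomised clusters.

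Reading the condition as the 2-year look-back before a cycle would make it harmless at the first cycle, but the words place it during follow-up.

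**Conclusion.** The rule is wrong as written. It contradicts its own intention-to-treat label and conditions the primary analysis on a consequence of treatment. For any true benefit, the expected bias is toward a CIR of 1.

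On the protocol's own inputs the size is modest: about one percentage point of PE or less under a uniform 68% reduction over 3 years. It becomes material with larger effects, lower transmission, shorter follow-up or full elimination in some villages. The largest losses rest on assumed shares of eliminating villages and on unadjusted fits. All the figures assume gamma-distributed rates with equal k in both arms, and treat a village with no symptomatic case as dropped.

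The point must still be fixed, because the rule defines the primary analysis set, passes to the secondary incidence outcomes, and does most harm when the trial succeeds. Power is only about 78–81% with every cluster kept.

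**What to change.** Replace the condition with wording such as: *All 30 randomised clusters will be analysed in the arm to which they were randomised; a cluster with no case during follow-up contributes a count of zero.* Apply the same set to the secondary incidence analyses. If the restriction is wanted at all, keep it as a labelled sensitivity analysis.

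The cost is one sentence in the protocol and analysis plan. No extra data are needed, and the specified model already takes zero counts. The change should be made and dated before the trial statistician and data analyst are unblinded.

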### Aims and objectives

The overall study objective is to evaluate the impact and safety of fMDA for *P. vivax* transmission reduction compared to no fMDA. The primary aim is to determine the effect of fMDA on the outcome of cumulative incidence of symptomatic, microscopy-confirmed *P. vivax* cases over the study period. *P. vivax* incidence will be determined based on the number of laboratory-confirmed, locally acquired cases reported from health facilities serving the catchment area of study villages. Secondary outcomes include incidence of *P. falciparum* or *P. vivax* and *P. falciparum* and infection prevalence and seroprevalence of *P. vivax* and/or *P. falciparum* measured in cross-sectional surveys (Table S1). Secondary aims are to assess the safety, tolerability, and acceptability of fMDA, as well as its cost-effectiveness compared to current standard-of-care interventions. Safety and tolerability outcomes will be measured as incidence of adverse events detected through active and passive pharmacovigilance and vomiting after administration. Acceptability will be measured as refusal rates and reported willingness to participate in future fMDA campaigns. Cost-effectiveness will be measured as cost per case averted, or per disability adjusted life year (DALY) averted. We hypothesize that fMDA will result in a greatly reduced latent hypnozoite reservoir and that will translate to reduced incidence, infection prevalence, seroprevalence, and cost-effectiveness compared to standard interventions and that it will be safe, well-tolerated, and acceptable to the community.

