**Fig. 1 Fig1:**
[figure not shown]
Flowchart demonstrating the involvement of FLAME communities throughout the trial per SPIRIT guidelines. Vector control includes the distribution of insecticide-treated nets (ITNs) and the use of indoor residual spraying (IRS). Symptomatic case management involves testing and treating confirmed malaria cases by microscopy or PCR testing at local health facilities or in the community by a community health worker. Outbreak response may include an active search strategy through screening and treatment of confirmed cases when malaria case incidence is increased significantly compared to the regular trend of cases for 2 consecutive weeks

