### Study setting and trial preparations

The trial will take place in Loreto Department, located in the Peruvian Amazon and where more than 90% of the country’s malaria cases occur [30]. Malaria transmission is perennial and historically peaks around April to June, though recently transmission has leveled out throughout the year. Based on national data from the first half of 2024, 82.5% of reported cases were *P. vivax* [30].

Communities or clusters will be eligible if they are located within 8 h of riverine or road transport of Iquitos. Villages with high (API > 250/1000) or sporadic transmission (< 2 cases) in the year prior to the trial, or extreme population size (> 650) will be excluded. A map of the study area and distributions of recent *P. vivax* annual parasite incidences (API) among communities in the region are shown in Fig. 3.

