#### Standard malaria interventions in the control and intervention arms

As part of the country’s national malaria elimination program, Plan Malaria Cero (Plan Malaria Zero) [26], standard malaria interventions will be provided in both study arms. Led by health promoters, these interventions include passive and active case detection at community members’ homes or at health establishments, microscopy at health establishments, and treatment per national policy guidelines. Tafenoquine (300 mg × 1) is registered in Peru as a radical cure for individuals that are G6PD normal and $$\ge$$ 16 years of age, but it is currently only available in pilot health facilities outside of the study area. Passive case detection detects symptomatic cases at health facilities. Active case detection up to 6–8 times per year involves village-wide searching for fever, followed by treatment of individuals testing positive by microscopy or rapid test. Vector control interventions include provision of Duranet insecticide-treated bed nets (1.5–1.7 people/net) impregnated with alpha-cypermethrin provided every 3 years on average and spraying with pirimiphos-methyl insecticide approximately 2 times per year (78.2% coverage of households in the Maynas Province of the Loreto Department).

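### The primary model is attached to all microscopy-confirmed cases, whereas the primary outcome is defined as symptomatic, microscopy-confirmed *P. vivax* cases

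*Protocol article*

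**What the plan says.** Three places in the protocol article fix the primary numerator.

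- **Aims and objectives:** "cumulative incidence of symptomatic, microscopy-confirmed *P. vivax* cases over the study period".
- **Identification of index cases and measurement of incidence:** "number of incident symptomatic microscopy-confirmed *P. vivax* malaria cases in residents divided by the total population".
- **Primary analysis:** "For the primary outcome of cumulative incidence of all microscopy-confirmed cases reported in study area residents", modelled by negative binomial regression on cluster-level counts with a population offset.

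The first two carry three conditions: symptoms, microscopy and *P. vivax*. The third keeps only microscopy and adds the word all. The abstract also names symptomatic *P. vivax* malaria as the primary outcome, and the sample size section powers the trial on *P. vivax* incidence alone. The Aims list *P. falciparum* incidence and combined-species incidence as secondary outcomes. The Secondary analyses section applies the primary approach to secondary incidence outcomes.

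On which cases could enter, the study setting section reports, from national data for the first half of 2024, that "82.5% of reported cases were" *P. vivax*. Routine active detection is described as "village-wide searching for fever, followed by treatment of individuals testing positive by microscopy or rapid test". The caption to Fig. 1 says: "Outbreak response may include an active search strategy through screening and treatment of confirmed cases".

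**The concern.** The only section that specifies the primary model gives it a different numerator from the one that defines the primary outcome. An analyst who follows that section literally would estimate an effect on all microscopy-confirmed malaria. That nearly duplicates the combined-species secondary outcome and is not what the trial was powered for.

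Two kinds of case outside the endpoint could then be counted. The first is non-vivax malaria. If fMDA affects it less than it affects *P. vivax*, counting it pulls the ratio towards 1 and costs power. The second is an asymptomatic microscopy-positive person found when outbreak response screens a village.

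The trial is also open-label. Two published definitions of the primary count leave room to choose between them once results are visible, or to be suspected of doing so.

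**Working it through.** **Inputs from the sample size section.** 15 clusters per arm, mean population 251, 3 years, control *P. vivax* rate 65 per 1000 per year, 68% reduction (ratio 0.32), k = 0.87, two-sided alpha 0.05, stated power 80%.

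**Step 1: reproduce the stated power.** The usual formula for comparing rates in an unmatched cluster trial is

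c = 1 + (z₀.₉₇₅ + z₀.₈₀)² × V, with V = [(λ₀ + λ₁)/y + k²(λ₀² + λ₁²)] / (λ₀ − λ₁)².

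Here λ₀ = 0.065, λ₁ = 0.065 × 0.32 = 0.0208 and y = 251 × 3 = 753 person-years per cluster.

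- (λ₀ + λ₁)/y = 0.0858/753 = 0.000114
- k²(λ₀² + λ₁²) = 0.7569 × 0.004658 = 0.003525
- (λ₀ − λ₁)² = 0.0442² = 0.001954
- V = 0.003639/0.001954 = 1.863
- c = 1 + 7.849 × 1.863 = 15.6 per arm
- Power with 15 per arm = Φ(√(14/1.863) − 1.96) = 78.3%, or 81.0% without the added 1

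The stated 80% is therefore reproduced, for *P. vivax* only.

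**Step 2: apply the Primary analysis wording literally.** Let s be the non-vivax share of control-arm cases and r the fMDA ratio for non-vivax cases. The all-species ratio is (1 − s) × 0.32 + s × r, and the all-species control rate is 0.065/(1 − s). The documents give neither s for the study villages nor r. The national share gives s = 1 − 0.825 = 0.175, and k is held at 0.87.

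For s = 0.175 and r = 1:

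- Ratio = 0.825 × 0.32 + 0.175 = 0.439, so the reduction reads as 56.1%
- λ₀ = 0.065/0.825 = 0.0788 and λ₁ = 0.0346. The absolute difference is still 0.0442, but both rates and their between-cluster spread are larger
- V = 2.946, and power = Φ(√(14/2.946) − 1.96) = 58.7%
- About 24 clusters per arm would be needed for 80% power

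| Non-vivax share s | Non-vivax ratio r | Reduction as read | Power |
|---|---|---|---|
| 5% | 1 | 64.6% | about 73% |
| 10% | 1 | 61.2% | about 68% |
| 17.5% | 1 | 56.1% | about 59% |
| 25% | 1 | 51.0% | about 49% |
| 17.5% | 0.66 | about 62% | about 69% |
| 17.5% | 0.32 | 68% | about 78% |

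**Step 3: counts.** Expected control-arm *P. vivax* cases over 3 years are 15 × 251 × 0.065 × 3 = 734. At the national share, the all-species count is 734/0.825 = 890, so about 156 cases would fall outside the endpoint.

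**Step 4: asymptomatic cases.** No arithmetic is possible. The document does not say how often outbreak screening occurs or what it finds.

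**The case against.** The strongest reply is that the wording is shorthand. The sentence points to a primary outcome already defined elsewhere, *P. vivax* is specified consistently in the abstract, aims, outcome section and power calculation, and a literal reading nearly duplicates a secondary outcome. The word all may refer to pooling recipients and non-recipients, which the Spillover effects section describes. This is plausible and lowers the chance that the wrong count is used. It does not remove the conflict, because the article itself treats species as a distinction between primary and secondary outcomes.

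Three stronger readings might be inferred, and the documents do not support them.

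- **That 56% is the expected result.** It is the no-effect case at a national species share. The section on fMDA in the intervention arm says that primaquine and tafenoquine have prophylactic and gametocytocidal effects against both species. With equal effects there is no dilution.
- **That asymptomatic cases would exaggerate the effect by a known amount.** Routine active detection searches for fever, survey infections are measured on dried blood spots, and asymptomatic survey cases are listed as index cases. Outbreak screening is the main route left. A rise in cases triggers it, so it could be unequal between arms, but equal proportional additions would leave the ratio unchanged and no figures are given.
- **That the Primary analysis wording loses symptomatic *P. vivax* cases diagnosed by rapid test.** The Aims and the outcome section already require microscopy, so a case without it is outside the endpoint under either wording. The looser laboratory-confirmed phrase in the Aims ("number of laboratory-confirmed, locally acquired cases reported from health facilities serving the catchment area of study villages") is a separate tension. Admitting rapid-test cases on PCR evidence would change the endpoint, not restore it.

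**Conclusion.** The point holds as a contradiction about the primary numerator: the model section drops the symptom and species conditions that define the outcome. This does not depend on any assumed figure and should be corrected.

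The consequence of a literal reading is uncertain. At a 17.5% non-vivax share with k unchanged, a true 68% *P. vivax* reduction would read as anything from 56% (power about 59%) to 68% (no loss), according to how far fMDA also reduces non-vivax malaria. If the local share is smaller, the dilution is smaller. The asymptomatic component is real under the literal wording, but narrow and unquantified. If the defined endpoint is used, the stated power stands.

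**What to change.** In the Primary analysis section, replace the reference to all microscopy-confirmed cases with symptomatic, microscopy-confirmed *P. vivax* cases, matching the Aims and the outcome-measurement section. Take symptom status from the case investigation already planned within 48 hours of diagnosis. Keep all-species incidence as a secondary outcome, and report any asymptomatic screen-detected cases separately.

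The cost is a wording change and slightly fewer counted events than under the literal wording. Nothing is lost against the design, which was powered on *P. vivax* alone.
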